## Introduction

1

Resting metabolic rate (RMR) constitutes the primary component of 24-h energy expenditure, representing the energy requirement for sustaining bodily functions while at rest in thermoneutral conditions (1). Given, fat-free mass (FFM) serves as a robust predictor of RMR in adolescent population (2, 3), exercise-induced weight loss is an important research topic since it leads to increases RMR by increasing the fat free mass component (4). However, studies in the adolescent population to modify the RMR have focused mainly on resistance or aerobic exercise (5, 6), without taking into account how regular physical activity (PA) might affect the RMR. Understanding PA energy expenditure (hereinafter referred to as PAEE) as the result of any muscular movement due to PA (7), the interaction of intensity, duration, and frequency of PA determines the total PAEE. In that sense, the American College of Sports Medicine states that exercise and health-oriented PA should be performed consistently to obtain its associated benefits. Nevertheless, nowadays there is an energy imbalance in the youth population, with high energy intake and low PAEE (8). This fact may have led to an increase in obesity in the young population worldwide, by 5.6% in girls and 7.8% in boys between 1975 and 2016 (9). In fact, the World Health Organization (WHO) has considered the overweight and obesity as a global public health concern (10). Although overweight and obesity have a multifactorial origin (9, 11), the literature recommends increasing PAEE through regular PA, as it is the most easily modifiable component of 24-h energy expenditure (11), to address the current situation. Therefore, interventions targeting young populations should aim to increase PAEE to restore or maintain energy balance (12).

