Therefore, this protocol describes the rationale and methodology of the ENERGY expenditure of school Commuting study (The ENERGYCO study). ENERGYCO project will address the gaps and limitations in the existing scientific literature regarding the PAEE that occurs during cycling to school. Considering the previous literature and existing gaps, the ENERGYCO project will be divided into two phases. Phase I will focus on using a portable metabolic system to assess PAEE associated with different modes of commuting (i.e., walking, cycling, motorized vehicles) under free-living conditions in Spanish adolescents. Additionally, Phase I will serve to develop a predictive equation that will be used in Phase II to measure PAEE associated with different modes of commuting to and from school. Additionally, considering the ongoing debate regarding the health benefits of ACS and the scarcity of studies examining the effects of school-based cycling interventions on RMR and PAEE, the Phase II will aim to assess the effects of a school-based cycling intervention on RMR and PAEE, as well as on other physiological (i.e., basal heart rate, blood pressure, and body temperature), physical (i.e., PA levels, anthropometric measures, body composition, physical fitness, and motor competence), and psychosocial outcomes (e.g., perceived barriers to active commute to school, self-esteem, and mental health) on Spanish adolescents. It is hypothesized that, in Phase I, using a portable metabolic system under free-living conditions will provide accurate and distinct measurements of PAEE associated with different commuting modes in Spanish adolescents. Specifically, we hypothesize that these measurements will highlight significant differences in PAEE across commuting modes, offering a more precise understanding of how commuting impacts adolescents’ physical activity levels. Additionally, we expect the data collected in Phase I to contribute to the development of a valid and reliable predictive equation for estimating PAEE during commuting to and from school. we hypothesize that a school-based cycling intervention will lead to a significant increase in both RMR and PAEE compared to a control group. We further hypothesize that the intervention will improve physiological outcomes (e.g., reductions in basal heart rate), physical outcomes (e.g., enhanced physical fitness and motor competence), and psychosocial outcomes (e.g., increased self-esteem) among Spanish adolescents.

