### Description and rationale of the ENERGYCO study

2.5

In Phase I the PAEE of different modes of commuting will be quantified by analyzing each participant individually in different controlled environments. For phase II, after recruiting schools and participants, an eight-week school-based cycling intervention will be implemented. The choice of an eight-week duration was based on the results reported in the systematic review by Dorothea et al. (47) on the effects of cycling interventions in a school setting. For example, although interventions lasting longer than 8 weeks demonstrate positive changes in physical fitness (43, 48), they also exhibit lower adherence, with a higher dropout rate among participants post-intervention. Therefore, considering that interventions lasting 4 to 8 weeks show effects on self-efficacy (49) or PA levels (50) and report a lower dropout rate, an eight-week duration was chosen for the school-based cycling intervention. The intervention will consist of adolescents having to cycle to and school for eight consecutive weeks. To encourage participants to complete the intervention, they will take part in a *Bikeability* training and different encouragement strategies will also be used during this period. Moreover, the ENERGYCO school-based cycling intervention shows relevant factors described in the current National Education Law for the curriculum of Compulsory Secondary Education. This approach is based on strategies proposed by the Active Living by Design Community Action Model (51), which involves preparing through the development of interventions, promoting education, and motivating students to cycle anywhere, as well as organizing activities with incentives and programs to engage participants. Regarding the control groups, participants in these schools will be asked to continue their daily habits. In addition, at the end of the eight-week cycling intervention in schools, control schools will be given the opportunity to conduct the *Bikeability* sessions and will receive all the motivational strategies used for the participating adolescents.

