##### Energy expenditure related to active commuting to school

2.7.1.2

PAEE related to different modes of commuting to school (i.e., walking, cycling, passive modes) will be measured using the Cosmed K5 portable metabolic system in Phase I. The Cosmed K5 has previously shown a good level of agreement compared to stationary metabolic carts at low cycling intensity (5.8% difference in VO_2_). At moderate intensities, it slightly underestimated VO_2_, VCO_2_, and energy expenditure (~6.6–6.9%). Additionally, during walking tests, the Cosmed K5 demonstrated high reproducibility, with a coefficient of variation of 4.5% for energy expenditure per kilometer and a concordance coefficient of 0.91. VO_2_ measurements were consistent, with low variability in the fraction of expired oxygen (coefficient of variation of 0.9%) (56). The Cosmed K5 is worn on the back with a harness and measures oxygen consumption (VO_2_) and carbon dioxide production (VCO_2_) in breath-by-breath mode. Before each assessment, the device will be calibrated using a reference gas mixture of 15.92% O_2_ and 5.03% CO_2_. Delay calibration for the breath-by-breath mode will also be performed (57). During the test, participants will breathe normally while commuting, and the Cosmed K5 will record data continuously. Data will be analyzed as the mean VO_2_ and VCO_2_ (ml/min) during each commuting mode. In Phase II, PAEE related to cycling will be estimated using predictive equations developed in Phase I. These equations will incorporate variables such as distance, speed, and heart rate, and will be cross-validated against PAEE measurements obtained with the Cosmed K5 to ensure accuracy. Therefore, data will be analyzed as the mean VO_2_ and VCO_2_ (ml/min) during each cycling trip to and from school, aggregated by participant during the intervention period.

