##### Trip characteristics

2.7.2.18

ACS behavior will be objectively evaluated over seven consecutive days using a Q-STARZ BT-Q1000XT GPS device, manufactured by Int Co., Ltd. (Taipei, Taiwan). The GPS will record distance, speed, and trip duration for each commute performed by the participants. Additionally, environmental variables such as terrain slope will be measured and later used as confounders in the analysis. The GPS will be configured with a 15-s epoch to ensure precise data collection. This protocol, which combines GPS data with accelerometry for analyzing ACS behavior, has been previously validated by our research group (17, 20, 31). In this project, the combination will also be used to estimate PAEE associated with different modes of commuting to school. The main variables of interest include distance (km), average speed (km/h), and trip duration (minutes). Data will be aggregated by participant and collected during baseline and follow-up assessments.

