#### Statistical analysis

2.10.2

Descriptive analyses of all study variables presented with the mean (standard deviation) and frequencies (percentage) will be performed. Subsequently, the normality of the variables will be analyzed using histograms and normality tests. In Phase I, for the comparison of PAEE between the different modes of commuting (i.e., walking, cycling, and motorized-vehicle), a repeated measures ANOVA will be performed using the per-protocol approach. In addition, Student t-test or Mann–Whitney tests will be performed to compare the fluctuation of PAEE according to speed or distance commuted between active modes of commuting (i.e., walking vs. cycling).Within Phase II, the effects of the school-based cycling intervention on RMR and other health-related outcomes will be studied using an analysis of covariance (ANCOVA). Post-intervention RMR and other-health related values will be included as dependent variables, group (i.e., experimental group vs. control group) as fixed factor, and baseline outcome data as covariates. To evaluate the effect of the intervention on the secondary outcomes (i.e., physiological, physical, and psychosocial outcomes), we will conduct the same analysis used for the main outcomes (i.e., ANCOVA analysis using the intention-to-treat approach). Moreover, to control the variability between schools, the analyses will include adjustments for contextual and organizational variables, such as the SES of the school area, the length of cycling lanes, the availability of bicycle parking, and the level of engagement of teachers and students in the intervention. The estimates will be present as raw and standardized (z-scores; i.e., mean differences between follow-up and baseline data divided by the standard deviation), as an indication of the change the post-intervention z-scores will be calculated relative to the baseline mean and standard deviation. Effect sizes will be categorized as small (0.2 SDs), medium (0.5 SDs), and large (0.8 SDs), based on Cohen (93). Finally, to analyze the influence of covariates on the association between the intervention and the main outcomes (i.e., RMR and PAEE), mediation analyses will be performed. The intervention will be included as the independent variable, and the main outcomes as the dependent variables. Covariates included in the mediation analysis will encompass body composition, physical function, cognitive determinants, perceived barriers or autonomy, built-environment characteristics, weather, among others. In the statistical analysis, a value of *p* < 0.05 will be considered statistically significant.

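### Phase II PAEE, a primary outcome, is defined per cycling trip during the intervention, which contradicts the baseline-adjusted comparison with controls planned for it

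*Protocol article*

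**What the plan says.** Table 3 lists resting metabolic rate (RMR) and energy expenditure as the primary outcomes, and section 2.10.2 calls RMR and PAEE the main outcomes. The Introduction hypothesises that "a school-based cycling intervention will lead to a significant increase in both RMR and PAEE compared to a control group".

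Section 2.7.1.2 is the only text under the primary outcomes that fixes the Phase II variable. It states that "In Phase II, PAEE related to cycling will be estimated using predictive equations developed in Phase I", with distance, speed and heart rate as example inputs. The quantity analysed is mean VO2 and VCO2 in ml/min "during each cycling trip to and from school, aggregated by participant during the intervention period". RMR, in section 2.7.1.1, is instead aggregated at baseline and follow-up.

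Section 2.10.2 models post-intervention values with group as fixed factor and "baseline outcome data as covariates". The per-protocol set in section 2.10.1, which carries the main results, requires valid data at both time points in both arms and gives RMR and PAEE as examples. For the control arm, section 2.5 says that "participants in these schools will be asked to continue their daily habits".

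Two places describe something wider. The Introduction says the Phase I equation will serve in Phase II for different commuting modes. Section 2.7.2.18 says that "ACS behavior will be objectively evaluated over seven consecutive days using a Q-STARZ BT-Q1000XT GPS device" and, with accelerometry added, that "the combination will also be used to estimate PAEE associated with different modes of commuting to school"; its data are collected at baseline and follow-up.

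**The concern.** A between-arm test needs a variable that exists in both arms, and baseline adjustment needs that variable before the intervention. A quantity built from cycling trips during the intervention meets the first need only for controls who happen to cycle, and the second for nobody. If the analysis were run on whoever has data, it would set intervention cyclists against a few self-selected control cyclists, and randomisation would no longer protect the comparison.

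The metric also differs from the hypothesis. The Introduction says that "the interaction of intensity, duration, and frequency of PA determines the total PAEE". A mean rate per minute carries intensity alone, so a programme that works by adding cycling trips could raise energy expenditure without moving the outcome.

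**Working it through.** **1. The definition against its uses**

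- Baseline: section 2.7.1.2 aggregates over the intervention period, so nobody has a baseline value. Section 2.10.2 needs one as covariate, and section 2.10.1 needs one for the per-protocol set.
- Control arm: a value exists only for a control who cycles to school. The hypothesis and the ANCOVA need values across the whole arm.
- Mode: section 2.7.1.2 covers cycling only. The Introduction and section 2.7.2.18 cover several modes.
- Instrument: section 2.7.1.2 uses a prediction equation. Table 3 ticks the Cosmed K5 for Phase II, and section 2.7.2.18 names GPS plus accelerometry.

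**2. How many controls could have a value**

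Inputs from section 2.4.2: 250 evaluable participants, 1:1 allocation, alpha 0.05, power 0.95, effect size 0.25 (read as Cohen's f).

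The plan's own figure comes first. With a noncentral F for two groups and one covariate, lambda = N × 0.25², 95% power needs N = 251 with 2 numerator degrees of freedom, which matches the stated 250. With 1 degree of freedom, the two-group contrast, it needs N = 210. Dropout gives 250 / 0.85 = 294.1, so 295, consistent with about 300. The present point does not depend on these figures; they only give 250 / 2 = 125 evaluable per arm.

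Table 2 excludes adolescents who cycled more than 3 days a week in the past year, so a control may cycle up to 3 days. Section 2.4.2 calls cycling prevalence low but gives no figure. The proportion p below is therefore an assumption.

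Controls with a value: n = 125 × p. For two equal groups d = 2f = 0.5. Without the baseline covariate, and treating adolescents as independent, power = Φ(0.5 / √(1/125 + 1/n) − 1.96).

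| p | n | Power |
|---|---|---|
| 0% | 0 | not estimable |
| 1% | 1.25 | 0.08 |
| 5% | 6.25 | 0.23 |
| 10% | 12.5 | 0.39 |
| 20% | 25 | 0.63 |
| all 125 | 125 | 0.977 |

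For example, at 20%: √(0.008 + 0.04) = 0.219; 0.5 / 0.219 = 2.28; 2.28 − 1.96 = 0.32; Φ(0.32) = 0.63.

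**3. What a mean rate leaves out**

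Trips over 8 weeks, assuming five school days a week:

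- every day, both ways: 5 × 2 × 8 = 80
- 3 days a week, both ways (Table 2 and section 2.8): 3 × 2 × 8 = 48
- 3 one-way trips a week (the loosest reading of the per-protocol rule in section 2.10.1, which accepts cycling to and/or from school): 3 × 1 × 8 = 24

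At equal pace and distance all three have the same mean ml/min. Energy spent on cycling differs by 80/48 = 1.7 or 80/24 = 3.3.

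**The case against.** The strongest reply is that the article already contains a workable PAEE. The Introduction and section 2.7.2.18 point to several commuting modes, the latter with baseline and follow-up data. Section 2.6.1 hands out the GPS and accelerometer without limiting them to one arm, and section 2.10.1 plainly expects PAEE twice in both arms. This largely stands. A reader might infer that PAEE exists only on cycling trips and cannot be analysed at all; the documents do not support that. They do support a contradiction. Section 2.7.2.18 lists distance, speed and duration as its main variables and does not redefine the primary outcome.

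The intention-to-treat analysis with imputation is no rescue for the variable in section 2.7.1.2: a baseline that is unobserved for everyone gives an imputation model nothing to work from.

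Other stronger readings also fail:

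- Nearly all controls lack a value. This is plausible, but no prevalence is given and up to 3 days of cycling is allowed, so only a range can be stated.
- The loss is 3.3-fold. That rests on the loosest adherence reading; cycling both ways on 3 days gives 1.7.
- The equation cannot be computed because GPS covers only seven days at a time. Its inputs are given as examples, and distance is also obtained from mapping software (section 2.7.2.17).
- Resting expenditure is not subtracted. The article does not say either way, and such detail may sit in the full protocol.
- The abstract promises daily PAEE. It speaks of daily energy expenditure; daily PAEE appears in the Introduction and Discussion.

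**Conclusion.** The concern holds as a contradiction in the definition of a primary outcome, and it must be resolved. Under section 2.7.1.2 the baseline is missing for every participant, which by itself blocks the ANCOVA of section 2.10.2. This part needs no assumption.

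The control-arm loss does rest on one: with 0 to 20% of 125 controls cycling, 0 to 25 have a value, and power at d = 0.5 is at most about 0.63 against 0.977 with full arms. Even that comparison would be among self-selected cyclists.

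Separately, the mean rate hides a 1.7- to 3.3-fold difference in energy spent, given equal pace and distance and a five-day school week. The variable therefore does not measure what the hypothesis is about.

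**What to change.** Define one Phase II PAEE variable for both arms: total school-commuting energy expenditure, in kcal per school day or per week, over all modes. Obtain it from the Phase I mode-specific equations applied to the seven-day GPS and accelerometer windows at baseline and follow-up. Time the windows identically in both arms and place the follow-up window inside the 8-week programme, for example in its last week; a window after the programme could miss the effect if cycling has stopped. Analyse follow-up on baseline by arm. Keep per-trip VO2 over the 8 weeks as a descriptive measure of exposure in the intervention arm.

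Align the Introduction, sections 2.7.1.2, 2.7.2.18, 2.10.1 and 2.10.2, and Table 3, including the Cosmed K5 tick for Phase II. Do not claim an effect on daily PAEE, as the Introduction and Discussion do, from this variable.

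The cost is mostly wording, because the equations, devices and seven-day windows are already planned. There is one real addition. Section 2.7.2.2 schedules only resting heart rate at baseline and follow-up, with trip heart rate during the intervention. If the equation uses heart rate, the strap must also be worn on commutes in both measurement weeks in both arms. Otherwise, use an equation based on mode, distance and speed. Settle this before baseline measurement, because trip heart rate not recorded then cannot be recovered.

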#### Secondary outcomes

2.7.2

##### Socio-demographic characteristics

2.7.2.1

Adolescents will self-report their gender, age, school grade, full postal address, socioeconomic status (including family education level and parents’ professions), extracurricular activities, and bicycle ownership through a structured questionnaire. Moreover, their parents will have to complete another questionnaire, where they will self-reported similar information to those previously self-reported by the adolescents. These data will be aggregated by participant and family, and they will be collected during baseline and follow-up assessments.

##### Heart rate

2.7.2.2

Heart rate will be monitored during three different commuting simulations in Phase I using the Polar Ignite H10 device (Polar Electro Oy, Kempele, Finland), which includes a chest strap and a watch. The Polar Ignite H10 has been considered the gold standard for measuring heart rate in sports conditions (with an RR interval mean bias ± limit of agreement of 0.2 ± 26.8 ms compared to a Holter monitor) (58). Data will be continuously recorded during the simulations and downloaded using the Polar app on a computer. The average heart rate (beats per minute) across the simulations will be calculated and aggregated by participant during baseline assessments. In Phase II, participants will measure their resting heart rate in the morning during the first weekend of both baseline and follow-up. Additionally, they will monitor their heart rate during each cycling trip to and from school throughout the eight-week intervention period. Data will be downloaded by the research staff using the Polar app after the follow-up period. The mean heart rate during cycling trips will be analyzed and aggregated by participant to examine trends over the intervention period.

##### Blood pressure

2.7.2.3

Blood pressure will be evaluated using a standardized protocol for children (59), that employs the auscultatory method. A stethoscope will be placed on the elbow flexure over the radial artery to determine systolic blood pressure (SBP) and diastolic blood pressure (DBP). Measurements will be conducted individually for each participant and averaged across three repeated assessments at baseline and follow-up.

##### Body temperature

2.7.2.4

Body temperature will be measured using an iButton device (DS-1922 L, Thermochron; resolution: 0.0625°C; Maxim, Dallas, USA) placed on the left wrist with an epoch of 1 s. During sports conditions, the iButton device observed error estimates were within acceptable limits for the skin temperature method comparison, with typical errors of <0.3°C (showing an r coefficient of >0.999 under all assessed conditions) (60). Data will be analyzed using the Temperatus software^2^ (61) and aggregated as the mean temperature over the recording period for each participant at baseline and follow-up.

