##### Weather

2.7.2.19

Ambient and weather conditions will be assessed using two complementary methods. In Phase I, ambient temperature will be measured using iButtons (S-1922 L, Thermochron; resolution: 0.0625°C; Maxim, Dallas, USA). Participants will wear an iButton attached to their trousers to measure outdoor temperature. It is important to note that the iButton device has also demonstrated a very high correlation with a mercury thermometer (r > 0.999) for measuring ambient temperature (REF). Data from the iButtons will be analyzed using the Temperatus software (see Footnote 2) (90). In Phase II, temperature (maximum, minimum, and average), total rainfall, and average wind speed will be obtained from the National Weather Data Bank. This open-source database contains climatological information recorded by observatories across the country. Data will be collected from the weather station closest to each school for the five weekdays and the preceding weekend prior to completing the student questionnaire. These variables will be recorded at both baseline and follow-up. The main variables of interest include daily ambient temperature (°C), total rainfall (mm), and average wind speed (km/h). Data will be aggregated by participant and city.

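### The secondary outcome called body temperature is wrist skin temperature: it supports no conclusion on body or core temperature, and the plan does not fix or adjust for the surroundings it depends on

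*Protocol article*

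**What the plan says.** The Introduction names "basal heart rate, blood pressure, and body temperature" as the other physiological outcomes on which the intervention's effect will be assessed. The Discussion repeats the list, and Table 3 enters body temperature as a secondary physiological outcome in both phases.

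Section 2.7.2.4 states: "Body temperature will be measured using an iButton device". The sensor is "placed on the left wrist with an epoch of 1 s". The supporting evidence is that error estimates were "within acceptable limits for the skin temperature method comparison", with typical errors below 0.3 °C. The analysed variable is "aggregated as the mean temperature over the recording period for each participant at baseline and follow-up".

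Section 2.7.2.19 uses the same type of device in Phase I as an environmental thermometer: "Participants will wear an iButton attached to their trousers to measure outdoor temperature". For Phase II it turns to station records: "Data will be collected from the weather station closest to each school", at baseline and at follow-up.

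Section 2.10.2 analyses secondary outcomes with the same ANCOVA as the main outcomes. The terms are group, the baseline value, and school-level adjustments illustrated by area socioeconomic status, cycle lanes, bicycle parking and engagement. Weather is named only among the covariates of the mediation analysis, which concerns RMR and PAEE.

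**The concern.** There are two separate issues.

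**The label.** A result reported under the name body temperature will be read as a statement about the body's thermal state. A single sensor at a peripheral skin site, supported only as a skin thermometer, cannot carry that statement. A difference between arms would tell the reader something about the skin of the wrist and no more.

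**The surroundings.** Skin temperature at the wrist responds to ambient temperature, clothing and local blood flow. Schools are the randomised unit. If schools are recorded in different conditions, everyone at a school shares that school's shift, and the model as described has no named term for it. The shift can then add noise or, with few schools, produce a chance difference between arms.

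**Working it through.** The plan states no figure on this point, so there is none to reproduce. The check sets the sections side by side and then sizes the weather issue under stated assumptions.

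**1. Label against measurement.** The outcome name is in the Introduction, the Discussion and Table 3. Section 2.7.2.4 gives one device, one site (left wrist) and one kind of validation (skin temperature). It describes no core site, no average over several skin sites and no conversion to body temperature. The quantity measured is wrist skin temperature.

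**2. Recording conditions.** Section 2.7.2.4 refers to a recording period without giving its length, setting or dates. The three assessment days described in section 2.6.1 do not mention the iButton. Figure 3, which outlines the assessments, is not reproduced in the text at hand and may show more.

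**3. Design features that protect the comparison.** Section 2.4.2 plans 1:1 allocation within each city, so each city has concurrent controls. Section 2.4.1 randomises schools after baseline, so baseline dates cannot depend on arm.

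**4. Size under assumptions.** The simulation has no true effect and uses an individual-level ANCOVA on arm and baseline:

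- baseline = e + w0
- follow-up = 0.5·e + r + w1

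Here e has variance 1 (within-school SD 1.0 °C) and r has variance 1 − 0.5² = 0.75. The shifts w0 and w1 are independent with SD τ. They are drawn once per city (shared weather) or once per school (own conditions). The test rejects when |t| > 1.97. There are three cities and 2,000 runs per cell, so the Monte Carlo standard error at 5% is √(0.05 × 0.95 / 2000) = 0.5 percentage points. The target sample is the protocol's 250. With equal school sizes that is 41 × 6 = 246, 20 × 12 = 240 or 8 × 30 = 240 participants. The within-school SD, the correlation of 0.5, τ and the numbers of schools are assumptions.

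False-positive rate at nominal 5%:

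| τ (°C) | Weather shared by city: 6 / 12 / 30 schools | Own conditions per school: 6 / 12 / 30 schools |
|---|---|---|
| 0 | 5% / 4% / 5% | 5% / 5% / 5% |
| 0.25 | 5% / 4% / 4% | 37% / 21% / 12% |
| 0.5 | 3% / 4% / 3% | 60% / 46% / 26% |
| 1.0 | 3% / 2% / 2% | 73% / 59% / 37% |

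Shared weather produces no false effect. School-specific conditions can produce one, more so with fewer schools.

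**5. Whether the weather data already collected fit.** The Phase II station data in section 2.7.2.19 cover the school week and weekend leading up to the student questionnaire. That window is tied to the questionnaire and not to the iButton recording. If recording takes place indoors, outdoor station temperature describes the wrong environment.

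**The case against.** The strongest reply is that the article discloses exactly what is measured: device, site and type of validation. It never says core temperature, so a reader might infer that the stated outcome goes unmeasured, and that would be too strong. Wrist skin temperature is measured, under a name that is too broad. This part of the reply stands.

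On weather, a reader might infer that the ANCOVA will mistake weather for an effect. The documents do not support that:

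- Nothing says that schools are recorded on different dates, and weather common to both arms of a city cancels.
- The adjustment list in section 2.10.2 is given as examples and does not exclude weather. Covariates for single outcomes are commonly left to the analysis plan.
- One can assume that wrist temperature moves 0.1 to 0.4 °C per 1 °C of ambient and that recording days differ by 5 °C. This gives 5 × 0.1 = 0.5 °C to 5 × 0.4 = 2.0 °C. Neither input is in the documents. Setting the result against the 0.3 °C sensor error shows little, because that figure is device accuracy and not an expected effect or a between-person spread.
- A school-level shift in an individual-level ANCOVA is a general matter for a cluster trial. It is not peculiar to this outcome, and a weather covariate would not settle it.

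Materiality is also small. This is one of many secondary outcomes, and the hypotheses in the Introduction do not name it.

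None of this removes the mismatch between the name and the measurement, or the dependence of a wrist reading on its surroundings.

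**Conclusion.** The point holds as a labelling and inference problem. As described, the outcome is mean wrist skin temperature, and the protocol offers no basis for a conclusion on body or core temperature. This rests on the document's own text and needs no assumption.

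The weather part holds only as a risk. It needs schools or arms to be recorded in different conditions, which the text neither states nor rules out. Under that premise and the assumed inputs above, the false-positive rate ranges from 12% (30 schools, shift SD 0.25 °C) to 73% (6 schools, shift SD 1.0 °C). With weather shared within each city it stays at 2% to 5%. The simulation shows why the recording conditions matter and is not an estimate for this trial.

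The consequence is minor: no primary conclusion depends on this outcome, and the remedy is cheap.

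**What to change.** - Define and report the outcome as wrist skin temperature in the Introduction, section 2.7.2.4, Table 3 and the Discussion, and draw no conclusion on body or core temperature.
- State the recording window and setting, and record both arms of a city in the same period and setting where feasible.
- Add ambient temperature on the actual recording days as a covariate for this outcome. Take station data for those days, since the window in section 2.7.2.19 precedes the questionnaire and has to be matched to the recording. If recording is indoors, use the indoor temperature instead.

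The cost is a narrower claim, a small data-matching task and one extra covariate. The station source is already in use, but indoor readings would have to be taken. The covariate guards against differing conditions and does not replace an analysis that allows for clustering by school.
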